## Abstract

**Background:**

Isometric resistance exercise training (IRT) involves sustained muscle contractions without changes in muscle length and joint angle, such as wall squats. Patients with hypertension may prefer IRT because they are easy to learn, require no equipment, are convenient, time-efficient, and can be performed anywhere. However, IRT have not shown to reduce blood pressure (BP) as detected by ambulatory BP measurements (ABPM), the reference standard for BP measurement. This study aims to examine the effectiveness of an IRT program in reducing BP.

**Methods:**

This randomized controlled trial (RCT) will involve 390 patients with a suboptimal daytime systolic BP of > 135–160 mmHg on a 24-h ABPM, who do not meet the current World Health Organization recommendations for physical activity. Participants will be randomly assigned to either the IRT (wall squat) group or stretching exercise (active control) group (1:1), using stratified and blocked randomization according to age (< 45, 45– < 60, and ≥ 60 years old), sex, and anti-hypertensive drug use (users versus non-users). Investigators will be blinded to randomization sequence and allocation. IRT group will receive a well-structured, widely accepted, and validated 24-week wall squat program (2 min per exercise, 2 min of rest between sets, and 3 sessions per week). Adherence will be monitored by regular patient communication via social media. The control group will receive the same treatment, with the exercise replaced by frequency-matched and time-matched stretching exercise. The primary outcome measure will be systolic daytime ABPM at 24 weeks. Secondary outcome measures will include other BP and ABPM parameters at 12 weeks, 24 weeks, and 12 months, carotid-femoral pulse wave velocity at 24 weeks and 12 months, and flow-mediated dilation at 24 weeks and 12 months. Safety data will be collected and reported.

**Discussion:**

This trial will be the first adequately powered RCT to determine whether IRT can be recommended as a treatment for hypertension, involving a Chinese population. It will also contribute new knowledge regarding the mechanisms of IRT. This research has the potential to influence clinical practices. If positive results are obtained, this research could potentially alleviate the substantial burden on healthcare systems caused by poor BP control.

**Trial registration:**

ClinicalTrials.gov NCT06510998. Registered on July19, 2024.

**Supplementary Information:**

The online version contains supplementary material available at 10.1186/s13063-026-09798-x.

## Protocol version {2}

Study protocol version 1 dated July 23, 2024.

## Introduction

### Background and rationale {9a}

Hypertension (HT) is the most prevalent chronic condition and is the leading cause of cardiovascular and renal morbidity and mortality [1]. Despite effective treatments, only approximately one-third of patients with HT have optimal control of their blood pressure (BP) [1]. Although anti-HT medications can effectively reduce BP, patients’ non-compliance to medications is prevalent globally (~ 40%), due to misconceptions (e.g., medications can cause renal damage) and psychosocial factors (e.g., forgetfulness) [2]. Similarly, patients have poor adherence to the effective aerobic and dynamic resistance exercises because additional time, skills, training venue, and equipment are required [3]. Conversely, isometric resistance exercise training (IRT), involving low intensity, sustained isometric exercise, can overcome these barriers because they are safe, time efficient (approximately 14 min per session, 3 sessions per week), easy to learn, and require little to no equipment [4]. Isometric exercise involves a muscle contraction with no change in muscle length and joint angle, contrasting with dynamic resistance exercise which involves repeated muscle shortening and lengthening. In clinical practice and research, the two most well-studied and well-structured IRT are the wall squat and hand grip exercise [4, 5]. Furthermore, when compared with other types of exercise, IRT carry no joint impact (lower risk of joint injury), have lower myocardial oxygen demand (less chest pain or ventricular arrhythmias and more suitable for patients with cardiovascular diseases), and require less space (more suitable for patients living or working in crowded areas or with limited mobility) [6, 7]. The latest 2023 network meta-analysis also found IRT most effective to reduce office BP (by ~ 8/4 mmHg) among all exercise modalities (e.g., aerobic/resistance training) in reducing office BP (by ~ 8/4 mmHg) [8].

An individual study demonstrated that IRT can effectively reduce 24-h BP on ambulatory BP monitoring (ABPM) [9]. However, a 2023 meta-analysis showed that IRT have not reduced 24-h BP or daytime BP on ABPM in patients with HT despite reducing office BP [5]. Although IRT have reduced night-time BP on ABPM, the results were highly heterogeneous and imprecise (systolic BP [SBP]: − 4.28 mmHg, I2 = 72.7%) [5]. As that meta-analysis described, the lack of definite improvement on ABPM has prevented wide implementation of IRT for HT patients because ABPM is consistently more reproducible, more predictive to cardiovascular outcomes and is the “gold” standard of BP measurements [5, 10, 11]. It is therefore unclear whether IRT truly reduced patients’ BP or only minimized white-coat effects. Currently, international guidelines recommended aerobic and resistance training and commented a lack of evidence for IRT [12, 13]. Furthermore, the anti-HT effects of IRT have been understudied in the Chinese population, and the recent systematic review has not identified any Chinese study [5, 14]. However, cardiovascular responses to exercise vary amongst ethnicities [15]. Because Chinese patients are more salt sensitive and physical exercise can reduce salt sensitivity, IRT may be more effective in reducing BP in Chinese [16, 17]. Wall squats may also be more implementable in Chinese because many of their daily activities are conducted in a squatting positing (i.e., the Asian squat) [18].

Furthermore, the mechanisms of BP reduction by IRT remain unclear. For instance, IRT (including wall squats) are hypothesized to partially occlude arteries (e.g., in the thigh and legs) by sustained muscle contractions and stimulate flow-mediated dilation (FMD) of vessels once the muscle contractions end. Therefore, progressive and repetitive exposures to IRT may enhance nitric-oxide mediated vasodilation and vessel diameters [5]. Although vascular changes and reduction in peripheral vascular resistance were hypothesized to be the main mechanisms of IRT, FMD or vascular stiffness (as measured by pulse wave velocity [PWV]) has yet shown to change after IRT in a 2023 meta-analysis due to limited studies [14]. Although IRT have been shown to improve heart rate variability (as an surrogate of autonomic nervous system activities), no included studies in the above two 2023 meta-analyses studied BP dipping status and 24-h BP variability (BPV), which are independent predictors to cardiovascular events and death [11, 19]. As BPV and BP dipping are determined by autonomic nervous system activities and vascular stiffness, these predictors to cardiovascular events may be improved by IRT [20, 21].

There are also important limitations in the existing relevant randomized-controlled trials (RCTs). (i) Although wall squat exercise may have superior hypotensive effect than hand grip, only 1 existing wall squat RCT (*n* = 48, lasted 4 weeks) measured ABPM [5]. (ii) The 4 existing relevant ABPM studies included in the 2023 meta-analysis were small, time-limited (≤ 12 weeks) and underpowered (*n* = 20 to 48, total *n* = 147), and recruited exclusively participants with normal ABPM BP (mean daytime BP < 135/85 mmHg) [5]. An ongoing Brazilian RCT (NCT03896334) lasting for 24 weeks is evaluating handgrip exercise rather than wall squat as in the present study. Third, as advocated by latest reviews, most RCTs had flaws in blinding of the assessors and allocation concealment, and no RCTs had monitored activities in the control group [5, 14]. Four, safety data is under-reported [4].

### Explanation for the choice of comparator {9b}

In the study design, stretching exercise was chosen for comparator. Previous meta-analysis showed that passive static stretching exercises did not change BP level in most RCTs and therefore can be active control in this RCT [22]. While there was no widely validated sham comparator or standardized control for isometric wall squat in RCTs, the use of passive static stretching exercises as a comparator will ensure that participants in both intervention and control groups perform some form of frequency-matched and time-matched interventions. This active control reduces potential bias related to passive controls. Details of the designs of control group is described in the Intervention and comparator section.

### Objectives {10}

The aim of the study is to investigate the effectiveness of the IRT in reducing BP of Chinese adults with sub-optimal BP, defined as a suboptimal daytime SBP of > 135–160 mmHg.

The objectives are to compare the effectiveness of wall squat exercise (intervention) and stretching (active control) for the following measures:To determine whether a 24-week IRT program leads to a reduction in daytime ABPM SBP compared to an active control group (primary objective)To assess the effects of IRT on 24-h, nighttime, and office BP at 12 weeks, 24 weeks, and 12 months after recruitment. This will provide data on the persistence of long-term daytime ABPM SBP reduction achieved through IRT at 12 months after recruitmentTo assess the effects of IRT on ABPM BP variabilities at 12 weeks, 24 weeks, and 12 months after recruitmentTo investigate the persistence of daytime ABPM SBP reduction achieved through IRT at 12 months after recruitmentTo evaluate whether IRT achieves BP reduction by improving vascular stiffness (measured through PWV) at 24 weeks and 12 months and endothelial function (measured through FMD) at 24 weeks and 12 months. Besides being potential mechanisms underlying BP reductions, PWV and FMD are also independent predictors to cardiovascular events [23, 24].To assess the safety and tolerability of IRT among patients with HT

## Methods: patient and public involvement, and trial design

### Patient and public involvement {11}

We conducted a pilot RCT on IRT, which included interviews exploring participants’ experience concerning the IRT intervention and trial design. The findings are used to modify the research question, study design, and recruitment and implementation phases.

### Trial design {12}

This protocol was written with reference to the Standard Protocol Items: Recommendations for Interventional Trials (SPIRIT) [25]. The SPIRIT checklist can be found in additional document 1. A parallel-arm (IRT vs. stretching exercise [active control]) RCT will be conducted in a 1:1 ratio. The primary objective is to determine whether an IRT program leads to a reduction in daytime ABPM SBP compared to an active control group at 24 weeks. Further data collection will be conducted at 12 weeks and 12 months post-recruitment to ensure safety and investigate long-term effects of the IRT program respectively (Fig. 1). Meditating and moderating roles of patients’ characteristics and secondary outcomes (e.g., FMD/PWV) to BP reduction by IRT will be investigated. The RCT was pre-registered on clinicaltrials.gov (NCT06510998) and was approved by the Joint Chinese University of Hong Kong-New Territories East Cluster Clinical Research Ethics Committee (2022.618). The study complies with the Declaration of Helsinki.

**Fig. 1 Fig1:**
[figure not shown]
Schedule of enrollment, interventions, and assessments

### Trial setting {13}

Participants will be recruited from the general public and primary care in Hong Kong by (i) direct recruitment of patients with HT by doctors/nurses and posters when they attended the publicly funded family medicine clinics (FMCs); and (ii) newspaper advertisements.

### Eligibility criteria for participants {14a}

Patients meeting all these criteria will be included: (i) a suboptimal daytime SBP of > 135–160 mmHg on a 24-h ABPM (the internationally recommended cut-off for elevated BP, the rationale for focusing on SBP is explained under “Outcomes”) [12]; (ii) reported no regular physical activity or less than that recommended for adults by the World Health Organization (e.g. < 150 min of moderate-intensity aerobic exercise per week); (iii) on stable doses of anti-HT medication(s) for ≥ 4 weeks if the patient is receiving drug treatments; (iv) agree for no drug changes during the intervention period (24 weeks); and (iv) aged ≥ 18 years old. Patients receiving or not receiving anti-HT drugs will be included to maximize external validity and investigate responders’ characteristics. Only patients with mildly elevated daytime SBP of > 135–160 will be included to ensure safety as drug changes are avoided as far as possible during the 24-week intervention period. Patients will be excluded if any of the following criteria are met: (i) cannot provide informed consent; (ii) unwillingness to repeat ABPM (primary outcome); (iii) relative contraindications to ABPM (i.e., diagnosed atrial fibrillation, night-time workers, occupational drivers, or patients with bleeding tendencies); (iv) severe osteoarthritis pending knee replacement surgery (these patients may be unable to perform the IRT (i.e., wall squat exercise)); (v) known secondary HT; (vi) use of ≥ 3 anti-HT medications at maximum doses or ≥ 4 anti-HT medications (these patients have resistant HT and represent another disease spectrum); (vii) SBP or Diastolic BP (DBP) are > 160 mmHg or > 100 mmHg, respectively, on ABPM at baseline or at 12 weeks follow-up to ensure safety (these patients require early treatment); (viii) pregnancy/breastfeeding; and (ix) active malignancy (Table 1).

**Table 1 Tab1:** Inclusion and exclusion criteria

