**Exclusion criteria**	
-Cannot provide informed consent	
-Unwillingness to repeat ambulatory blood pressure monitoring (primary outcome)	
-Relative contraindications to ambulatory blood pressure monitoring (i.e. diagnosed atrial fibrillation, nighttime workers, occupational drivers, or patients with bleeding tendencies)	
-Severe osteoarthritis pending knee replacement surgery (these patients may be unable to perform the IRE (i.e. wall squat exercise))	
-Known secondary hypertension	
-Use of ≥ 3 anti-hypertensive medications at maximum doses or ≥ 4 anti-hypertensive medications (these patients have resistant hypertension and represent another disease spectrum)	
-Systolic blood pressure or diastolic blood pressure are > 160 mmHg or > 100 mmHg, respectively, on ambulatory blood pressure monitoring at *baseline or at 12 weeks follow-up to ensure safety* (these patients require early treatment)	
-Pregnancy/breastfeeding	
-Active malignancy	

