## Outcomes, data collection, and management

### Outcomes {16}, plans for assessment, and collection of outcomes {25a}

After data collection at baseline, participants will return for outcome assessments at 12 weeks, 24 weeks, and 12 months. Details of the time point for outcomes and trial instruments are specified in each outcome below. All research assistants who are involved in data collection will be trained the correct use of instruments (e.g., ABPM) and questionnaires, as well as retrieval of data. After each assessment, the files will be reviewed to identify missing or erroneous data. Any missing information will be retrieved immediately from the instruments and the study participants.

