### Plans to promote participant retention and complete follow-up {25b}

Participants are given supermarket coupons after they completed data collection at each timepoints (i.e., baseline, 12 weeks, 24 weeks, and 12 months) to reinforce participant adherence to the trial and data collection. Also, regular communication will be maintained with participants to promote adherence to the trial and complete follow-up. Data of participants at all timepoints will be collected even after the withdrawal of the interventions, with their consents. For participants who discontinue the trial, reasons for withdrawal will be obtained.

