### Who will be included in each analysis {27b}

All randomized participants will be included in the analysis.

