### How missing data will be handled in the analysis {27c} and methods for additional analyses (e.g. subgroup analyses) {27d}

In our funding proposal, we initially stated that “the analysis will be conducted on an intention-to-treat basis (primary analysis) and a per-protocol basis (sensitivity analysis).” However, per the European Medicines Agency (ICH E9[R1]), these terms can be ambiguous, and relevant estimands should be employed [53]. In this RCT, we anticipate intercurrent events (ICEs) such as changes in medications during the first 24 weeks, non-adherence to interventions, severe illnesses that prohibit participants to perform exercises (as described above), and switches between intervention groups. For our primary analysis, we will utilize the “treatment policy” estimand, which treats the occurrence of ICEs as irrelevant and uses the actual observed values for the outcome variable [53]. This approach aligns with our previous intention-to-treat analysis. For our secondary analysis, we will adopt the “hypothetical strategy” estimand, which estimates outcomes assuming all patients in their respective groups adhere perfectly to the interventions [53]. Additionally, missing data will be addressed through multiple imputation [54, 55].

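### The 12-week ABPM limit sits in the eligibility exclusions although it is read after randomisation; the protocol does not say how this fits with analysing everyone randomised under treatment policy

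*Protocol article*

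**What the plan says.** The section on eligibility criteria for participants {14a} lists, as exclusion (vii), ambulatory BP above 160 mmHg systolic or 100 mmHg diastolic, "respectively, on ABPM at baseline or at 12 weeks follow-up to ensure safety (these patients require early treatment". Table 1 repeats it under the exclusion criteria: "baseline or at 12 weeks follow-up to ensure safety".

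The outcomes section {16}/{25a} shows that week 12 is a follow-up visit: "After data collection at baseline, participants will return for outcome assessments at 12 weeks, 24 weeks, and 12 months".

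On the analysis set, section {27b} reads "All randomized participants will be included in the analysis". Section {27c}/{27d} sets a treatment-policy primary estimand, which "treats the occurrence of ICEs as irrelevant and uses the actual observed values for the outcome variable". The intercurrent events it names are medication changes in the first 24 weeks, non-adherence, illness severe enough to stop the exercise, and switching between groups.

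The discontinuation criteria {15b} mention serious illness and voluntary withdrawal, with no BP limit. The retention section {25b} says: "Data of participants at all timepoints will be collected even after the withdrawal of the interventions, with their consents".

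**The concern.** An eligibility criterion settles who enters the trial, so it can only use information available before randomisation. The 12-week ABPM is a later reading of the same variable as the primary outcome, and the intervention is meant to change it. If staff follow exclusion (vii) as written, a participant over the limit at week 12 leaves the trial and may have no 24-week ABPM. The primary analysis would then lose outcomes selectively, on a variable that treatment affects. No later analysis document can recover readings that were not taken.

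The protocol gives two instructions for the same person, excluded in one place and analysed in another, and no sentence connects them. The matter is current: the trial status section reports 190 of 390 recruited, the first in April 2025.

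**Working it through.** **1. The passages side by side, for a participant who crosses the limit at week 12**

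| Place | What it implies |
|---|---|
| Exclusion (vii) and Table 1 | Excluded |
| Discontinuation {15b} | Not mentioned |
| Retention {25b} | Data still collected if this counts as withdrawal of the intervention, with consent |
| Analysis set {27b} | Included |
| Estimand {27c} | Observed value used; a drug change is a listed intercurrent event, crossing the limit is not |

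The last three rows agree with each other. The first agrees with them only if excluded means withdrawn from the exercise phase for safety but followed up, which the text does not say.

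**2. The protocol's own sample size**

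Inputs from section {19}: difference 3 mmHg, SD 10 mmHg, power 0.80, error rate 0.05 (used as two-sided type I error), dropout 10%.

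n per arm = 2 × (1.960 + 0.842)² × 10² / 3² = 174.4, rounded up to 175. Then 175 / 0.90 = 194.4, rounded up to 195 per arm, or 390 in total. This reproduces, so the point is not a sample-size error.

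**3. Size of the effect if these participants were dropped**

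From the protocol: baseline limited to 135–160 mmHg, SD 10, true effect 3 mmHg, ANCOVA of 24-week SBP on baseline and arm, and removal if 12-week SBP exceeds 160. Assumed, because the document does not give them: mean SBP of 140–150 mmHg before the baseline limits are applied, correlation between visits of 0.5–0.8, and the full effect present at both week 12 and week 24. The diastolic limit is not modelled. Simulation error in each estimate is about 0.02 mmHg.

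| Mean, correlation | Controls over 160 | IRT over 160 | Per 195 (control, IRT) | All kept | Dropped |
|---|---|---|---|---|---|
| 140, 0.8 | 1.9% | 0.7% | 3.7, 1.4 | 3.02 | 2.97 |
| 140, 0.5 | 2.7% | 1.2% | 5.2, 2.4 | 2.98 | 2.90 |
| 145, 0.7 | 5.0% | 2.2% | 9.7, 4.3 | 3.02 | 2.88 |
| 150, 0.7 | 9.7% | 4.8% | 18.9, 9.3 | 2.99 | 2.76 |
| 150, 0.5 | 12.3% | 6.9% | 24.0, 13.5 | 2.99 | 2.73 |

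Attenuation is about 2% to 9%. For example, 1 − 2.73/2.99 = 8.7%. With no true effect (mean 145, correlation 0.7), 5.0% of controls and 4.9% of IRT participants are removed and the estimate is about 0.01 mmHg both with and without them.

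**4. If they are kept but receive early drug treatment**

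If everyone crossing receives a drug that lowers SBP by D, the treatment-policy estimate is about 3 − D × (control share − IRT share). With D = 8 mmHg (assumed, not in the document):

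- 140, 0.8: 3 − 8 × (0.019 − 0.007) = 2.90
- 145, 0.7: 3 − 8 × (0.050 − 0.022) = 2.78
- 150, 0.5: 3 − 8 × (0.123 − 0.069) = 2.57

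**The case against.** The strongest reply is that nothing states these participants leave the analysis. The criterion gives safety and early treatment as its reason, the analysis-set sentence has no exceptions, and data collection continues after the intervention is withdrawn. If early treatment means a drug change, that is already a listed intercurrent event handled by treatment policy. This stands as a coherent reading, so the text is better called unreconciled than impossible to follow. What does not stand is the idea that the protocol adopts this reading: the rule is in the eligibility list, and neither the discontinuation nor the retention section refers to it.

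Multiple imputation, also planned, could keep such participants formally in the analysis. It is not a full answer. Imputing from participants who stayed under the limit does not give the value observed after any early treatment, which is what treatment policy asks for.

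Two stronger readings are tempting:

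- **Power falls below 80%.** The document does not support this. Section {19} does not say whether the 10% dropout already covers these losses. If SD 10 describes a single reading, ANCOVA also has a smaller residual SD. At correlation 0.7 the simulated residual SD is 7.1, so power with all 175 kept is about Φ(3/7.1 × √(175/2) − 1.96) = Φ(1.99) = 0.98. After dropping (mean 145), n = 175 × (1 − 0.036) = 168.7 and power is about Φ(2.88/7.1 × √(168.7/2) − 1.96) = Φ(1.77) = 0.96. A shortfall appears only under less favourable assumptions, such as SD 10 with no gain from the baseline adjustment.
- **The rule necessarily removes more controls and biases the trial.** The imbalance requires both that participants are dropped and that IRT lowers BP by week 12. With no effect there is no bias, so false-positive risk is not clearly affected.

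**Conclusion.** The point holds as an unresolved conflict about who contributes to the primary analysis. A post-randomisation, treatment-affected reading is used as an eligibility exclusion in two places, and the protocol does not link it to its all-randomised, treatment-policy analysis.

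The numerical consequence is conditional and modest: 0.05 to 0.26 mmHg off a 3 mmHg effect, always towards zero, if those crossing are dropped and IRT works by week 12. It rests on means and correlations that the document does not supply, and on the systolic limit only. The case for change therefore rests on the contradiction and on the risk of losing 24-week readings, not on the size of the bias. Keeping these participants need not return the estimate to 3.0 mmHg. What it secures is an intact randomised comparison and a defined estimand.

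**What to change.** Reconcile sections {14a}, Table 1, {15b}, {25b}, {27b} and {27c}:

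- Limit the eligibility exclusion to the baseline ABPM.
- Move the 12-week limit, with its value and clinical handling unchanged, out of the eligibility list to where post-randomisation events are described.
- State that crossing it is an intercurrent event under treatment policy, that 24-week and 12-month ABPM are still collected with consent, and that the participant is analysed in the assigned arm.
- Report the number crossing at week 12 by arm.
- Seek 24-week ABPM for any participant already removed under this rule. The document does not say whether there are any.

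The cost is a protocol amendment, with ethics approval and a registry update, and ABPM visits that are already scheduled. The downside is that the treatment-policy estimate will include the effect of any early drug treatment. Controls may receive it more often, so the observed difference may be below the effect of the exercise alone.
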